## Abstract

**Introduction:**

The Lancashire and Cumbria Innovation Alliance (LCIA) Test Bed is a partnership between the National Health Service in England, industry (led by Philips) and Lancaster University. Through the implementation of a combination of innovative health technologies and practices, it aims to determine the most effective and cost-effective ways of supporting frail older people with long-term conditions to remain well in the community. Among the Test Bed’s objectives are to improve patient activation and the ability of older people to self-care at home, reduce healthcare system utilisation, and deliver increased workforce productivity.

**Methods and analysis:**

Patients aged 55 years and over are recruited to four cohorts defined by their risk of hospital admission, with long-term conditions including chronic obstructive pulmonary disease, dementia, diabetes and heart failure. The programme is determined on an individual basis, with a range of technologies available. The evaluation is adopting a two-phase approach: phase 1 includes a bespoke patient survey and a mass matched control analysis; and phase 2 is using observational interviews with patients, and weekly diaries, action learning meetings and focus groups with members of staff and other key stakeholders. Phase 1 data analysis consists of a statistical evaluation of the effectiveness of the programme. A health economic analysis of its costs and associated cost changes will be undertaken. Phase 2 data will be analysed thematically with the aid of Atlas.ti qualitative software. The evaluation is located within a logic model framework, to consider the processes, management and participation that may have implications for the Test Bed’s success.

**Ethics and dissemination:**

The LCIA Test Bed evaluation has received ethical approval from the Health Research Authority and Lancaster University’s Faculty of Health and Medicine Research Ethics Committee. A range of dissemination methods are adopted, including deliberative panels to validate findings and develop outcomes for policy and practice.

Strengths and limitations of this studyThe evaluation is considering both the effectiveness, in terms of measures such as hospital admissions, and cost-effectiveness of the Test Bed.The protocol evaluates the potential for patient activation through health technology.Observational interviews with patients in their own homes enable insights into how older people experience and engage with the technology.For both the Test Bed participants and controls, the evaluation has to use proxy measures of the costs incurred to the National Health Service.Due to the timescale of the overall programme, it is not possible to assess the longer term impact of the programme.

## Introduction

In the UK, increasing numbers of older people are living with long-term conditions (LTCs) including diabetes, chronic obstructive pulmonary disease (COPD), heart failure and dementia.^1^ This is contributing to increased pressure on health and social care systems, including accident and emergency services, which in turn increases demand on the number of hospital beds.^2^ At the same time, local authorities are experiencing a reduction in the funding available to provide social care.^3^

Concerns about this so-called care gap and our future ability to cope with the growing numbers of older people with LTCs underpin governmental drivers to develop new models of care within vanguard sites^i^ that are cost-effective and that facilitate older people’s ability to better self-manage their care needs at home. The NHS England Test Bed programme has thus been designed to encourage the trialling of new models of care that are supported by health technologies across a number of areas in the UK.

This paper reports on the protocol for the evaluation of one such programme, the Lancashire and Cumbria Innovation Alliance (LCIA) Test Bed in the North West of England. The programme commenced on 1 April 2016 and is due to be completed on 30 June 2018.

### The LCIA Test Bed initiative

The LCIA Test Bed^ii^ is a partnership between the National Health Service (NHS), industry (led by Philips) and Lancaster University, and is one of seven Test Beds located across England. Two neighbouring vanguard sites, part of the Lancaster Health Hub (an established NHS/university partnership comprising 10 local organisations), will deliver the Test Bed. The Test Bed’s aims and objectives are presented below.

#### Test Bed aim

To determine the most effective and cost-effective ways of supporting frail older people with dementia and other LTCs to remain well in the community and avoid unnecessary hospital admissions.

#### Test Bed objectives

To use a combinatorial range of technologies and services to:better support frail older people, living with LTCsimprove patient activation^iii^ and the ability of older people with a range of LTCs to self-care at homeimprove health awareness and outcomes for older people with LTCsreduce healthcare system utilisation and increase productivity within the healthcare workforce.

Over 2 years, the Test Bed is implementing a combination of innovative technologies and practices aimed at supporting these aims and objectives. The clinical challenge is to reduce hospital admissions, create capacity, reduce overall costs, minimise other health and social care usage, and maximise patient outcomes for a targeted population of older people (defined in this Test Bed as those aged 55 years and over) who suffer a range of LTCs including dementia. These LTCs present a major challenge for the area given its dispersed population, and innovative solutions are urgently required.

The main technology partner is Philips, which together with a number of small-sized and medium-sized enterprises, social enterprises and voluntary organisations is working with the Test Bed to introduce a health technology-enabled supported self-care programme.^iv^

The two vanguard sites include the Fylde Coast and North Lancashire, with the technologies being provided in addition to the new models of care being implemented by these two sites. The Fylde Coast Vanguard^v^ is drawing on the extensive care model, which brings together a range of services in the same location to achieve a coordinated team of healthcare professionals, with patients each allocated a well-being support worker.^4^ This model focuses on multispecialty community providers, moving specialist care out of hospitals and into the community.^5^ The North Lancashire Vanguard, Better Care Together, sees healthcare professionals working together in partnership to help people manage their own health conditions.^6^ This model focuses on integrated primary and acute care settings, joining up general practitioner (GP), hospital, community and mental health services.^7^ Further details of these new models of care are set out in the NHS England ‘Five Year Forward View’^8^ and by the Nuffield Trust.^9^

As part of the LCIA Test Bed programme, these existing services are being combined with innovative technologies and support for older people with LTCs including COPD, heart failure, diabetes and dementia. For those with lower levels of risk in cohort 3 (see table 1), asthma and hypertension will also be included. The focus of this Test Bed is to empower patients to actively manage their health conditions and change behaviour through the provision of appropriate technologies, coaching and education.

**Table 1 T1:** Recruitment criteria for the four Lancashire and Cumbria Innovation Alliance Test Bed cohorts

Cohort	Age	Risk of hospital admission (%)	Long-term conditions
Cohort 1	Aged 55 years or over	>25	Chronic obstructive pulmonary disease, heart failure
Cohort 2		>10 and <25	
Cohort 3		<10	Diabetes, asthma, chronic heart disease, hypertension
Cohort 4		NA	Early-stage dementia (Addenbrooke’s Cognitive Examination-III assessment tool)

NA, not applicable.

A core part of the programme also focuses on increasing involvement of the third sector and community organisations in providing support for the Test Bed model, and understanding the impact of the service on staff and key stakeholders.

### Core outcomes for the evaluation

The Test Bed focuses on a combinational approach to technologies. Hence, rather than focusing on the impact of any single technology, the Test Bed evaluation is focusing on how health technologies as an addition to existing vanguard services can improve and promote self-care at home and reduce hospital admissions for older people with LTCs.

The evaluation is focusing on three primary outcomes:the extent to which supported self-care telehealth technology can improve patient outcomes, through reduced hospital admissions, medication, GP visits, home visits and community service usethe extent to which supported self-care telehealth technology can improve patient activation for frail older people with LTCsthe cost-effectiveness of the programme and how it might be scaled up to provide better value for patients and taxpayers.

Secondary outcomes include the following:identification of the strengths and weaknesses of the programme and how these may be built on or addressedassessment of patient/staff perceptions of how the new service improves on existing services and makes best use of voluntary and community servicesassessment of the impact of the new service within the healthcare workforce in terms of communication between care teams, productivity, capacity, coordination of care and work satisfaction.

To achieve these, we are:using quantitative and qualitative measures to examine benefits to patients and patient outcomes as identified aboveundertaking an economic evaluation of the impact of adding a combination of technologies to support and promote self-care in the provision of healthcare in comparison with standard care with cohorts 1 and 2 (see table 2)drawing on a logic model to demonstrate how to construct the service as a scalable model that might provide better value to patients and taxpayers.

**Table 2 T2:** Lancashire and Cumbria Innovation Alliance Test Bed cohort sample sizes

Cohort	Total population (%)*	Total patients	Frail and elderly patients (%)	Patients with dementia (%)	Patients estimated to be appropriate for the service (n)	Appropriate patients within cohort that will be recruited within the Test Bed period (%)	Minimum number of patients recruited within Test Bed period	Estimated number of patients by the end of the Test Bed period
(Age >55, risk >25% and 1 LTC)	1.70	5262	20	3.5	1737	30	521	500
(Age >55, 10%< risk <25% and 1 LTC)	3.00	9286	4	1.1	3064	15	460	500
(Age >55, risk <10% 1 of a broader set of LTCs)	9.20	28 477	2	1.6	9398	5	470	500
(Diagnosis of dementia)	0.79	2430		100.0	810	10	81	100

(*Combined over a population of approximately 310 000 people) (see Acknowledgements).

LTC, long-term condition.

## Methods and analysis

### Ethical approval

The overall evaluation involves two distinct phases: phase 1 involves collection of survey data designed to evaluate any change in health and health-related behaviours in patients using the combinatorial technologies; and phase 2 involves understanding the impact and experiences of patients using the technologies, and the impact on working practices among members of staff involved in the delivery of the technologies. Following discussion with the Health Research Authority (HRA) and the Research and Development Directors of the NHS Trusts involved in the programme, it was agreed that phase 1 was service evaluation and as such did not require HRA approvals. Phase 2 however was deemed by the HRA to be gathering new data and was thus defined by them as ‘research’, therefore requiring HRA approvals (Integrated Research Application System (IRAS) Project ID: 208395). Further details about the two phases are provided below.

Phase 2 of the evaluation has also been adopted onto the National Institute for Health Research portfolio.^vi^

### Sampling and recruitment

Patients are being recruited to four cohorts defined by their risk of hospital admission. The LTCs are noted above and are outlined in table 1.

Participants for cohorts 1, 2 and 3 are being recruited to the Test Bed through the vanguard services to which they are already assigned. As illustrated in table 1, cohort 4 is focusing specifically on patients with early-stage dementia. Potential participants for cohort 4 are being recruited through the Memory Assessment Service (MAS) in the Fylde Coast and North Lancashire. In the diagnosis of dementia, these services use the Addenbrooke’s Cognitive Examination-III (ACE-III) assessment tool to focus on five cognitive domains. People who have received a recent diagnosis of mild dementia by a consultant psychiatrist following their comprehensive assessment with the MAS are deemed as having fulfilled the entry criteria of mild dementia. For these patients, the ACE-III or Mini-ACE has been completed as part of their cognitive assessment at the MAS clinic, the results of which have aided the formulation of the dementia diagnosis. Only patients judged by a clinician to have mild dementia are invited to take part in the Test Bed.

All patients consenting to take part in the Test Bed and receiving the technology are required to participate in some aspect of phase 1 of the service evaluation and will sign a consent form. Specifically, primary outcomes 1, 2 and 3 will be evaluated for cohorts 1 and 2, and primary outcomes 1 and 2 will be evaluated for cohorts 3 and 4. Participation in phase 2, the qualitative phase of the evaluation, is optional. Patients indicating an interest in participating in phase 2 are being consented separately through a two-stage consent process.

The sample size for recruitment to each cohort has been informed by population and risk data for the area, along with the methodology used in a previous study.^10 11^ As table 2 illustrates, the overall aim of the Test Bed is to recruit 1600 patients; however, given the anticipated challenges of recruitment and potential attrition due to the nature of the patient group, we estimate an overall recruitment and retention figure of 60% (overall n=960).

Allowing for a phased increase in recruitment, the overall recruitment is estimated at approximately 60%–70% of the figures identified in table 2. This will provide sufficient data from cohorts 1 and 2 to demonstrate a change in hospital admissions (a primary outcome). Cohorts 3 and 4 will not be assessed for this outcome, although other measures of well-being, patient activation and loneliness will be used to describe these cohorts. The secondary outcomes are being supported by observational interviews across all four cohorts.

### The programme

The patient interface varies across the four cohorts, and the technologies available to people within the different cohorts are presented in table 3. A patient’s programme is determined on an individual basis and is informed by a number of factors, including health condition(s), personal preferences and other needs. Some patients are using different technologies at different periods of time within the 6-month programme.

**Table 3 T3:** Technologies available to each cohort

Cohort	Company	Technology	Description
1 and 4	Philips	Motiva*	A telehealth platform that operates through a tablet or television (TV) set top box interface that connects wirelessly to a range of telemonitoring equipment in the home (eg, wireless weighing scales, blood pressure metres, pulse oximeters and thermometers)
	MKS Solutions Limited	SpeakSet†	A video calling system that connects a health professional with a patient through the patient’s TV in their own home
	NHS Stoke-on-Trent Clinical Commissioning Group’s Licence	Florence/NHS Simple‡	A short message communication software providing a reminder/communication text messaging service for patients
1, 2 and 3	Cambridge Cognition Limited	CANTAB Mobile§	An assessment tool designed for healthcare professionals to identify the earliest signs of clinically significant memory impairment. The assessment comprises three tests: the Paired Associates Learning test to assess episodic memory; the Geriatric Depression Scale to identify signs of depression; and an activities of daily living questionnaire to assess functionality in daily life.
2	Intelesant Limited	Intelesant¶	A mobile app to support daily management of chronic obstructive pulmonary disease through SMS text messaging alerts for coaching, prompts and reminders. It incorporates the individual’s action plan in response to changes in symptoms.
	Philips	Personal Blood Pressure Cuff**	A blood pressure monitor that works in conjunction with the Philips Suite App to enable a patient to record their blood pressure
2 and 4	Philips	Health Watch††	A health watch that tracks heart rate and other cardio condition metrics, and monitors activity, sleeping patterns and nutrition behaviour (not a sports watch). It is best paired with a smartphone running the Philips Suite App.
3	uMotif Limited	uMotif‡‡	A health app available as a mobile app, digital tool or wearable device to capture data through a graphical interface and help patients track and understand their health and symptoms. It provides a health report, connects to other wearable devices, sends medication reminders, and keeps track of regular tasks and daily activities.
4	National Museums Liverpool	House of Memories§§	A health app that enables people living with dementia and their carers/families to keep a record of objects and experiences from the past. Patients and/or carers can create their own memory tree, memory box or memory timeline.

*http://www.philips.co.uk/healthcare/solutions/enterprise-telehealth/home-telehealth.

†http://www.speakset.com.

‡http://www.simple.uk.net.

§http://www.cambridgecognition.com.

¶http://www.intelesant.com.

**http://www.philips.co.uk/c-m-hs/health-programs/upper-arm-blood-pressure-monitor.

††http://www.philips.co.uk/c-m-hs/health-programs/health-watch.

‡‡http://www.umotif.com.

§§http://www.liverpoolmuseums.org.uk/learning/projects/house-of-memories/.

In summary, the LCIA Test Bed provides a structured programme of case management, monitoring, education and coaching supported by a clinical hub. It thus involves clinical and non-clinical teams, community involvement and community feedback. Good Things Foundation^vii^ is providing support to patients regarding their digital skills to help them use the innovator technologies.

### Evaluation design

A requirement of this evaluation^viii^ was that it adopts a rapid cycle approach to enable the delivery of the programme to be adapted and amended in the light of feedback received from patients and clinicians. As a result, a randomised controlled trial design was deemed unsuitable.

To address the core aims and objectives outlined above and the NHS England requirements, the evaluation was designed as a longitudinal, mixed-method evaluation, to include the following:

Phase 1:a bespoke patient survey incorporating validated toolsa mass matched control analysis.

Phase 2:phased observational interviews with patientsweekly diaries, action learning meetings and focus groups with staff and other key stakeholders.

The two phases of the evaluation design are adopting different sampling and recruitment strategies, along with methods, as set out below. Each has its own participant information sheets, consent forms and, where applicable, schedules (eg, for the interviews and focus groups). A separate flyer has been designed for patients with dementia, providing information about the study in an informative and accessible manner, drawing on images and large font. In all instances, it will be made clear to patients that they can be supported by a carer or other family member should they wish. It is anticipated that all participants in cohort 4 (mild dementia) will be accompanied by a carer or other family member.

All materials developed for the evaluation and submitted to ethical review were shared and informed through discussion with patient by experience groups (including those with dementia), a clinical reference group and an evaluation advisory board. Feedback and comment from these three groups were taken into account in finalising the documents submitted for ethics approval.

#### The patient survey

##### Recruitment and informed consent

In line with referral to the service, recruitment is being staggered over the programme period. Only patients judged by a clinician to have an acceptable level of cognitive function to give informed consent are invited to take part in the Test Bed. The impact of the programme on each participant is being evaluated over a 6-month period. Final recruitment to the evaluation will thus be at the end of month 15, to allow for the 6-month programme and a 3-month period for final analyses. All patients recruited into the Test Bed and receiving the service are included in the quantitative (service evaluation) stage and are completing the phase 1 consent form. Patients in phase 1 are completing a baseline, mid (12 weeks) and endpoint (24 weeks) survey during the 6-month programme.

##### Methods

The data analysis consists of a statistical evaluation of the effectiveness of the programme and a health economic analysis of its costs and associated cost changes for cohorts 1 and 2. The evaluation is collecting anonymised information for each participant concerning age, gender, ethnicity, living arrangements, education completed, and use of healthcare services in the 4 weeks before completing the questionnaire such as hospital services (inpatient care, outpatient visits and Accident & Emergency visits), primary care services, social care services and medicines. In all cohorts, validated instruments for use with older people to assess health-related quality of life, health and well-being and patient activation are being used (each of which can be completed by proxy if required): Warwick-Edinburgh Mental Well-being Scale, EQ-5D-5L, Patient Activation Measure-13 and the De Jong Gierveld Loneliness Scale. These tools are reapplied at weeks 12 and 24.

The evaluation team are working with the technology innovators^ix^ to minimise the demands of the evaluation on patients. Participants are also being offered the option of completing the questionnaires on paper or by telephone.

Drawing on Hospital Episode Statistics data, the primary outcomes for cohorts 1 and 2 will be evaluated against a matched control group (3 controls to 1 Test Bed patient). This will be coordinated in conjunction with the Midlands and Lancashire Commissioning Support Unit.

For cohorts 1 and 2, the cost-effectiveness analysis of the programme will assess the costs per hospital admission avoided. For the Test Bed patients and for the control group, the mean of hospital admissions will be estimated. The primary outcome is the difference between the change in the two groups, which will be estimated using linear regression adjusted for the matching covariates. Ninety-five per cent CIs will be reported for all estimated coefficients. A sensitivity analysis for key parameters will be undertaken.

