#### The mass control group

The evaluation team will match three control subjects per programme participant for cohorts 1 and 2, the controls being sampled from the same vanguard sites as those on the Test Bed. In terms of contamination between control and Test Bed groups, obtaining control data from the Commissioning Support Unit ensures no controls are also members of the Test Bed. The matching will be performed using the following variables: predicted probability (risk) of hospital admission, LTC, gender and age. The predicted probability of hospital admission for each participant and control will be calculated using the combined predictive model.^12^ The matching will be performed using a standard multivariate matching algorithm (Mahalanobis distance matching). The aim of matching on these variables is to obtain a control group which has similar characteristics for these variables compared with the programme participants. This should help minimise any possible confounding effects of these variables.

The statistical analysis is conducted using the statistical software Stata (V.14).

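### The primary change-in-admissions analysis neither matches nor adjusts for baseline admissions, so a temporary excess among participants would read as a reduction; a baseline-adjusted estimate should be reported beside it

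*Protocol article*

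**What the plan says.** The design is not randomised: under Evaluation design, "a randomised controlled trial design was deemed unsuitable". Participants in cohorts 1 and 2 enter through vanguard services that already look after them, and they must consent. Three controls per participant are drawn from the same vanguard sites through the Commissioning Support Unit.

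The analysis is fixed under The patient survey, Methods, using Hospital Episode Statistics (HES): "For the Test Bed patients and for the control group, the mean of hospital admissions will be estimated", and the primary outcome is then "the difference between the change in the two groups, which will be estimated using linear regression adjusted for the matching covariates". The covariates are listed under The mass control group: "The matching will be performed using the following variables: predicted probability (risk) of hospital admission, LTC, gender and age". On the risk score that section says: "The predicted probability of hospital admission for each participant and control will be calculated using the combined predictive model". It does not say what goes into the model. The benefit it expects from matching is limited to confounding by the listed variables.

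The same Methods section makes cost per hospital admission avoided the cost-effectiveness measure for these cohorts. It promises a sensitivity analysis for key parameters without naming them.

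**The concern.** A change in admissions needs a pre-index count. That count enters the outcome with a coefficient fixed at −1, and it appears nowhere else: not in the matching set and not among the covariates. Nothing in the design makes participants and controls with the same predicted risk equal on recent admissions.

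Admission counts over short periods are noisy. If participants tend to join after an unusually bad spell, their counts will fall back by more than their controls' counts, and the planned estimate reads the extra fall as a programme effect. The error favours the programme. It would carry into a primary outcome and into the denominator of the cost per admission avoided.

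**Working it through.** **Figures in the plan.** The article gives no admission rate, standard deviation, pre/post correlation or HES baseline window, so there is no calculation on this point to reproduce. Its sample size arithmetic does reproduce: 500 + 500 + 500 + 100 = 1600, and 1600 × 0.60 = 960. For cohorts 1 and 2, 60% to 70% of 500 + 500 is 600 to 700 participants, hence 1800 to 2100 controls.

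**How the two estimates are related.** Use the same patients and matching covariates throughout. Let d be the adjusted group difference in pre-index admissions and b the slope of post-index on pre-index admissions within group, given the covariates.

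- Post-index difference without baseline = baseline-adjusted estimate + b·d.
- Change-score estimate = that difference − d.
- Hence change-score estimate = baseline-adjusted estimate − (1−b)·d.

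This is an identity of least squares. Which estimate is right depends on why d is not zero:

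- *Temporary excess:* the adjusted estimate is right and the change score is off by −(1−b)d.
- *Stable unmeasured difference:* the change score is right and the adjusted estimate is off by +(1−b)d.

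With d > 0 and b between 0 and 1, a mixture of the two puts the truth between the estimates. With d < 0 the signs reverse.

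**Size for an assumed temporary excess d = 0.10 admissions per patient:**

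| b (assumed) | −(1−b)·d |
|---|---|
| 0.2 | −0.8 × 0.10 = −0.08 |
| 0.3 | −0.7 × 0.10 = −0.07 |
| 0.5 | −0.5 × 0.10 = −0.05 |

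**Simulation 1: no true effect, enrolment related to recent admissions.** Assumptions: 600 participants and 1800 controls; Poisson counts with mean 0.25 per period and log-normal frailty (log SD 0.8); 1:3 nearest matching on a noisy risk score; log-odds of enrolment raised by 0.3 per recent admission; 40 runs per row.

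| Risk score uses prior admissions | d | Change score | Baseline-adjusted | False positives (change / adjusted) |
|---|---|---|---|---|
| not at all | 0.098 | −0.090 | −0.005 | 72% / 7% |
| moderately | 0.072 | −0.076 | −0.010 | 57% / 5% |
| strongly | 0.049 | −0.053 | −0.006 | 30% / 5% |

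With 40 runs the false-positive rates are rough: √(0.72 × 0.28 / 40) ≈ 0.07 for the first. With enrolment unrelated to recent admissions, the change score averaged 0.002 to 0.007, so there was no bias.

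**Simulation 2: no true effect, the selection mechanism varied.** Assumptions: 300 participants, 900 matched controls, mean about 0.35 to 0.41 admissions, pre/post correlation about 0.35 to 0.39.

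| Enrolment depends on | Change score (95% CI coverage) | Baseline-adjusted (coverage) |
|---|---|---|
| recent admissions (weight +35% each) | −0.151 (31%) | +0.002 (94%) |
| stable frailty not in the score | +0.005 (92%) | +0.089 (52%) |
| both | −0.067 (76%) | +0.070 (68%) |

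**Simulation 3: a separate null run at 600:1800.** It shows the same pattern. Under selection on recent admissions the change score gave −0.142 (5% coverage), or −0.057 (73%) when the score carried prior admissions. Under stable unmeasured frailty the change score gave +0.004 and the adjusted analysis +0.104 (10% coverage).

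**The case against.** The strongest reply is that a difference in change between non-randomised groups is a recognised design, difference-in-differences. It is chosen precisely to remove stable unmeasured differences, which are likely when patients enter through clinical services and must consent. This stands. A reader might infer that baseline adjustment is the correct primary analysis and the change score an error. The second row of simulation 2 shows why that goes too far: adjustment can hide a real benefit as readily as the change score can invent one.

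Second, the article nowhere says that patients join after a recent admission. It would be tempting to conclude that the planned result will be biased, or that controls do not regress to the mean. Neither is supported. Matched controls regress too, and only a differential fall matters. The enrolment weights above are assumptions, and without them the bias disappears.

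Third, the risk score may already reflect admission history. The article does not say. In simulation 1 this reduced the bias from −0.090 to −0.053 but did not remove it, because matching on a composite score does not balance each component.

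Fourth, a reader might take linear regression to mean classical standard errors that ignore the matched sets. The article does not say so, and that detail can reasonably sit in the analysis plan.

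The promised sensitivity analysis does not answer the point, since its parameters are not named.

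**Conclusion.** The point holds as an unprotected risk, not as a demonstrated bias. The text fixes a change score adjusted only for risk, long-term condition, gender and age. A temporary excess d of recent admissions among participants would then move the estimate by about −(1−b)d towards apparent success, and nothing specified in the article would reveal it. Under the assumed settings of the three simulations, that shift ran from −0.053 to −0.151 admissions per patient. The real size depends on d, b and the content of the risk score, none of which the article gives.

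Baseline adjustment has the opposite weakness, so neither estimate is safe alone. Together they bracket the effect between the two selection mechanisms. The change score is also less precise: its variance relative to the adjusted analysis is 2/(1+r), or 1.67 at r = 0.2 and 1.33 at r = 0.5 for pre/post correlation r. That is a loss of efficiency, not of validity.

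**What to change.** Before the HES outcome data are analysed:

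1. State the pre-index window, and report pre-index admissions in participants and matched controls over it. This estimates d directly. If d is near zero, the two analyses coincide and the concern falls away.
2. Keep the change-score estimate. Prespecify beside it an analysis of post-index admissions with the pre-index count as a covariate, on the same matched sample. If the count is instead added to the matching variables, do so in a separate match for this second analysis. Adding it to the only match would push d towards zero, make the two estimates agree by construction, and lose the protection against stable differences.
3. Treat the two estimates as a bracket. State in advance what counts as agreement, and claim a reduction and a cost per admission avoided only if both agree.
4. As a minor addition, use robust standard errors or cluster them on the matched set.

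The pre-index counts are already needed to compute change, so no data or patients are added. The cost is one more analysis and a less clear-cut conclusion if the estimates disagree. If the re-matching option is used, the match on age and risk becomes slightly looser.
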